### Implementation of interventions

An integrated, multifaceted package of interventions will be implemented in the intervention practices by research coordinators who have been trained in the use of the interventions. The GPs in the control practices will continue normal clinical practice while the GPs in the intervention practices will be trained in the interventions as described below. In the six month study period, the research coordinators will regularly visit the intervention practices to support uptake of the interventions and provide any necessary supplementary training.

### Interventions

Evidence based interventions already demonstrated to be effective at reducing antibiotic prescribing for ARIs elsewhere in the world were selected [33]. They were combined into an integrated, multifaceted package with the following components:*Poster on Practice Antibiotic Prescribing Policy*This intervention consists of displaying a poster-sized prescribing policy in the GPs waiting room and/or examination room. GPs are encouraged to insert their photograph as endorsement on the poster. The poster, written at the eighth grade reading level in English emphasises the GPs’ commitment to guidelines, i.e. *Therapeutic Guidelines: Antibiotic*, [35] for appropriate antibiotic prescribing and explains why antibiotics are not appropriate in many cases [18].*Patient information leaflet*The leaflet provides information to the patient about inappropriate use of antibiotics for ARIs and the potential harmful effects of antibiotics. It complements the poster in the GPs waiting room and/or examination room.*Online communication training package*An online communication module is offered in combination with background information on the problem of antimicrobial resistance in primary care and the effectiveness of antibiotics for most commonly presenting ARIs. The module is based on the GRACE INTRO study [19] and has been adapted carefully for the Australian context as part of the Changing the Antibiotic Prescribing of General Practice (ChAP study) (https://www.anzctr.org.au/Trial/Registration/TrialReview.aspx?id=366836&isReview=true), a controlled trial funded by Therapeutic Guidelines Ltd (http://www.tg.org.au/index.php?sectionid=505).The online communication training is targeted at GPs rather than patients, and is developed to be sensitive to cultural and national differences. The training in enhanced communication skills focuses on exploring patients’ concerns and expectations, providing information on symptoms, natural course of the disease, treatments, agreement of a management plan, summing up, and providing guidance about when to re-consult. GPs are also provided with a booklet [36] for use during consultations that includes information on symptoms, use of antibiotics that are concordant with *Therapeutic Guidelines: Antibiotic* [35] and antibiotic resistance, self-help measures, and when to re-consult. The training is supported by video demonstrations of consultation techniques and is offered as a Continuing Professional Development activity to GPs.*Delayed antibiotic prescribing*The GP can offer the patient a delayed antibiotic prescription. This consists of advice to the patient to only fill the prescription at a pharmacy after a few days if symptoms are not starting to settle or become more severe [37]. A sticker is made available to GPs to apply to the prescription, labelling it as a delayed prescription.*Patient Decision Aids*A brief graphical laminated summary of evidence for the management of a number of ARI conditions is provided as a decision aid for use during the consultation. These decision aids have been developed to assist GP and patient to make an appropriate decision about the management of the condition. The Patient Decision Aids support the following conditions:acute sore throat;acute rhinosinusitisacute otitis media; andacute bronchitis*Near patient testing: CRP study*The CRP test is widely used in some European primary care settings [38] and has been shown to significantly reduce antibiotic prescribing for patients with ARIs [39].The intervention practices will each have access to a CRP testing machine for three months (with 50 CRP tests per practice provided free of charge) to determine the feasibility and uptake of this type of near patient testing.Tests will be performed using the QuikRead CRP kits (Orion Diagnostica). The research co-ordinator, in conjunction with the distribution company (ABACUS ALS), will train the GPs and practice staff in the use and interpretation of the tests. In addition GPs will have access to an online training module on CRP testing (http://gaps.uq.edu.au).The following instructions will be provided regarding CRP testing:CRP testing should only be used within ARI consultations for lower respiratory tract infections and acute rhinosinusitis.The GP can decide to perform a CRP test as a complement to the routine consultation (including history and physical examination).The CRP test is performed on a finger prick blood sample and the result will be available within a few minutes.The CRP test result can be used in addition to the clinical assessment to decide whether to prescribe an antibiotic.

### Sample size

The sample size calculation for this study was based on the average change in antibiotic prescription rates in practices in the intervention group (before – after the intervention) compared to the average change in practices in the control group over the same period. For example, an average change in antibiotic prescription rate from 40 to 20 % in the intervention practices and no change in the control practices would result in a difference of 0.2 between the two groups. A difference in average change in rates in the range 0.20–0.25, if the standard deviation in rates was about 0.2, was considered clinically significant and plausible. With equal numbers of practices in the two groups, power of 80 %, significance level of 5 % for a two tailed test, for a difference of 0.24, 12 practices per group would be needed. In fact 14 practices per group were recruited so that a difference of 0.22 would be detectable.

### Recruitment

General practitioners who have consented to participate in the study have been recruited from the selected general practices. General practice staff and patients attending the recruited GP practices for consultation with non-infectious complaints and who have consented to the point prevalence study of asymptomatic carriage of bacterial upper respiratory pathogens have also been recruited.

### Randomisation

Practices were randomly assigned to either the intervention or control arm in a 1:1 ratio. A blocked randomisation list with 8 practices per block was generated using the online software package Sealed Envelope Ltd. 2015 available from: https://www.sealedenvelope.com/simple-randomiser/v1.

### Data collection

In Australia the universal health insurance scheme, Medicare, provides access to medical and hospital services for all Australian residents and some visitors. It includes the Medical Benefits Scheme (MBS) which subsidises the costs of all visits to GPs and medical specialists in non-hospital settings, and the Pharmaceutical Benefits Scheme (PBS) which covers almost all medicines. MBS data include individual records for every patient encounter with a GP; GPs are identified by individual provider codes. PBS data include individual records of every prescription dispensed - from July 2012 this covers all prescriptions, regardless of government subsidies. The prescribing GP is identified by an individual prescriber number. There are legislative constraints on linking MBS and PBS records, but de-identified records can be obtained from the Department of Human Services. For all consenting GPs (in the intervention and control practices) provider records will be obtained for each patient encounter billed to the MBS and prescriber records for each prescription reported to the Pharmaceutical Benefits Scheme (PBS; from July 2012 this covers all prescriptions, regardless of government subsidies). Data will be requested from July 2012 to the end of the intervention period. The data will be extracted a month after the conclusion of the intervention phase in order to ensure that all records have been submitted Department of Human Services. Each prescription will be coded using the Anatomical Therapeutic Chemical (ATC) and those coded J01 (antibacterial for systemic use) are the outcomes of primary interest. Prescription rates will be estimated from the number of antibiotic prescriptions per GP in a specific period (e.g. day or week) and the number of patient encounters for that period and GP as the off-set (i.e., a measure of activity or ‘exposure’).

The cost of the package will be estimated from the perspective of the public health system at the conclusion of the intervention phase of the study. All resources used in implementing the package, including both consumable items and time for all personnel involved, will be identified. Allocation of GP time and practice specific items will be estimated based on responses to questions in the semi-structured interviews. Data on consumables and all centralised staffing will be measured retrospectively by the project co-ordinator using a pre-developed costing spreadsheet. Resources invested in any materials already developed will be considered sunk costs and not included in the cost of the intervention. Resources used solely for research and evaluation purposes will also not be included. Resources will be valued in 2016 Australian dollars using local market prices and labour costs to give a total cost of implementation.

We will also estimate the economic value of the change in antimicrobial usage that results from the package using PBS list prices. This will be combined with our data on the cost of implementing the package to provide a measure of the total changes in costs achieved.

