**Methods/design:**

This is a cluster randomised trial comparing two parallel groups of general practitioners in 28 urban general practices in Queensland, Australia: 14 intervention and 14 control practices. The protocol was peer-reviewed by content experts who were nominated by the funding organization.

This study evaluates an integrated, multifaceted evidence-based package of interventions implemented over a six month period. The included interventions, which have previously been demonstrated to be effective at reducing antibiotic prescribing for acute respiratory infections, are: delayed prescribing; patient decision aids; communication training; commitment to a practice prescribing policy for antibiotics; patient information leaflet; and near patient testing with C-reactive protein.

In addition, two sub-studies are nested in the main study: (1) point prevalence estimation carriage of bacterial upper respiratory pathogens in practice staff and asymptomatic patients; (2) feasibility of direct measures of antibiotic resistance by nose/throat swabbing.

The main outcome data are from Australia’s national health insurance scheme, Medicare, which will be accessed after the completion of the intervention phase. They include the number of antibiotic prescriptions and the number of patient visits per general practitioner for periods before and during the intervention. The incidence of antibiotic prescriptions will be modelled using the numbers of patients as the denominator and seasonal and other factors as explanatory variables. Results will compare the change in prescription rates before and during the intervention in the two groups of practices.

Semi-structured interviews will be conducted with the general practitioners and practice staff (practice nurse and/or practice manager) from the intervention practices on conclusion of the intervention phase to assess the feasibility and uptake of the interventions.

An economic evaluation will be conducted to estimate the costs of implementing the package, and its cost-effectiveness in terms of cost per unit reduction in prescribing.

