### Data analysis

Prescription rates will be estimated using generalised linear models (e.g., Poisson regression) for the number of antibiotic prescriptions per GP in a specific period (e.g., day or week) with the number of patient encounters for that period and GP as the off-set (i.e., a measure of activity or ‘exposure’). The explanatory variables will be included in the model to account for: intervention vs control practices; periods before and during the intervention; and temporal variables to account for secular trends and seasonal effects. The models will be multi-level to account for nesting of patients within GPs and GPs within practices.

Cost-effectiveness of the package will be estimated from the perspective of the public healthcare system. Results will be presented as the net cost of implementation and as the cost per unit reduction in prescription rates. It is unclear what Australian decision makers are prepared to pay for a unit reduction in prescribing so results will be compared to cost-effectiveness estimates published in the international literature to gauge the efficiency of this package relative to other approaches used to reduce GP prescribing. Standard sensitivity analyses (one-way and probabilistic) will be used to explore the robustness of conclusions to uncertainty in the underlying data.

Semi-structured telephone interviews will be conducted with the GPs and practice staff, including practice nurses and/or practice manager, from the intervention practices, after the intervention phase of the study Questions will focus on the acceptability and feasibility of the interventions, including the near patient testing (CRP study) in the practice and perceived impact on the management of ARIs. Interviews will be conducted after the full package has been implemented. All interviews will be recorded digitally and transcribed verbatim by the interviewer. Interview data will be analysed using inductive thematic analysis. Two researchers will independently code the interviews, compare their coding and discuss discrepancies. The final thematic framework will be constructed through an iterative process and tested by researchers with clinical expertise.

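### Antibiotic savings are valued at PBS list prices although the stated perspective is the public payer's, so any patient-paid amount counts as a public saving

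*Protocol article*

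**What the plan says.** Four statements in the protocol article bear on this.

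- **Perspective.** Methods, Data collection: "The cost of the package will be estimated from the perspective of the public health system". Methods, Data analysis, for the evaluation as a whole: "Cost-effectiveness of the package will be estimated from the perspective of the public healthcare system".
- **Unit price.** Methods, Data collection: "We will also estimate the economic value of the change in antimicrobial usage that results from the package using PBS list prices".
- **Volume.** The same section says of the PBS records: "from July 2012 this covers all prescriptions, regardless of government subsidies".
- **How the saving is used.** The same section: "This will be combined with our data on the cost of implementing the package to provide a measure of the total changes in costs achieved". The outputs are then given under Data analysis: "Results will be presented as the net cost of implementation and as the cost per unit reduction in prescription rates".

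Data analysis also plans one-way and probabilistic sensitivity analyses, directed at uncertain inputs.

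**The concern.** A perspective determines whose money counts. Under a public-payer perspective, an avoided prescription is worth what the government would have paid for it. A list price is a price for the item. It equals the government's outlay only if the item is subsidised and the patient pays none of it. The document itself says that its records do not depend on subsidy, so the counted volume can include items on which the public payer spends nothing.

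The valued change in usage is offset against the implementation cost, so the mismatch passes directly into net cost. If prescribing falls, the error can go only one way, towards making the package look cheaper to the public payer. The abstract says that the cost-effectiveness results are to inform policy on national implementation, and for that reader the public outlay is the figure of interest.

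**Working it through.** The economic sections give no figures, so there is none to reproduce. The check is algebraic, with assumed ranges for what the document does not give.

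**Symbols, all assumed because the document gives no values**
- n: prescriptions avoided
- u: share of these with no government subsidy
- p: mean list price of subsidised items
- r: mean price of unsubsidised items divided by p
- c: patient's share of the price on subsidised items
- C: implementation cost

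**Step 1, saving as planned (list price on every record).** S = n p [(1-u) + u r]

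**Step 2, saving to the public payer.** G = n p (1-u)(1-c)

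**Step 3, overstatement factor.** F = S/G = [(1-u) + u r] / [(1-u)(1-c)]

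With r = 1 and c = 0 this reduces to 1/(1-u). With positive prices, F equals 1 only if u = c = 0, and otherwise exceeds 1.

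**Step 4, numbers**

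| u | r = 1, c = 0 | r = 0.5, c = 0 | r = 1, c = 0.25 |
|---|---|---|---|
| 0 | 1.00 | 1.00 | 1.33 |
| 0.3 | 1/0.7 = 1.43 | 0.85/0.7 = 1.21 | 1/0.525 = 1.90 |
| 0.5 | 1/0.5 = 2.00 | 0.75/0.5 = 1.50 | 1/0.375 = 2.67 |

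Cheaper unsubsidised items pull the factor down. A patient share on subsidised items pushes it up.

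**Step 5, effect on net cost.** Reported net cost is C - S. Net cost to the public payer is C - S/F. The understatement is S(1 - 1/F), which is 0.5 S at F = 2. At that value, any C between 0.5 S and S would be reported as a public saving when it is a public loss. Neither C nor S is in the document, so this shows what could happen and does not predict it.

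**The case against.** The strongest defence has four parts.

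1. **Records counted and records costed need not be the same.** The statement about subsidy describes coverage of the outcome data. The costing text speaks of a change in usage and does not say how unsubsidised records are treated. This is fair as a limit on certainty. But no exclusion or reduced price is stated, and the one price source named is the list price.

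2. **The perspective is first attached to the package cost, and the drug valuation is introduced separately.** This does not stand. Data analysis puts cost-effectiveness as a whole on the public perspective, and the two amounts are combined.

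3. **Sensitivity analyses are planned.** Varying uncertain inputs around a base case does not correct a base case priced from another perspective.

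4. **The size is unknown and the outcome is secondary.** Both are true. The factor applies to the gross drug saving only, and its effect on net cost depends on how large that saving is relative to the implementation cost. This limits the weight of the point without removing the contradiction.

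A reader might also infer that the cost-effectiveness ratio is itself wrong, because the costing step ends in a total ("using local market prices and labour costs to give a total cost of implementation") while the effect is a rate per encounter. An undivided total over a rate difference would indeed depend on the size of the programme. The document does not say that this is the calculation. It defines neither the scale of the numerator nor the unit of reduction, and the abstract's phrase, "its cost-effectiveness in terms of cost per unit reduction in prescribing", fits cost per prescription averted equally well. If cost is put on the same per-encounter basis, the ratio equals cost per prescription averted and is scale-free. A journal article commonly leaves such detail to the full plan, so it is no error here.

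**Conclusion.** The point holds for the valuation of the drug saving. The stated perspective, the price source and the record coverage do not fit together. Followed as written, they overstate the public drug saving and understate net cost whenever prescribing falls and any avoided item is unsubsidised or partly paid by the patient.

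The direction follows from the document's own statements. The size does not. The 1.4-fold and 2-fold figures are illustrations that rest on assumed unsubsidised shares of 0.3 and 0.5, equal average prices and no patient share on subsidised items. It would be tempting to call 1/(1-u) a minimum, but the document does not support that: at u = 0.5, unsubsidised items at half the price give 1.5-fold.

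The effect is confined to the economic evaluation, a secondary objective.

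**What to change.** In the base case, value the change in usage at the government benefit paid per PBS record, with zero for records that carry no subsidy. Show full list price as a sensitivity analysis, labelled as a payer-plus-patient perspective. If the benefit paid cannot be obtained (the article does not list the extract fields), declare the wider perspective for the drug-cost component and say so wherever net cost is reported. Either course makes Data collection and Data analysis agree.

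The cost is one more data field and a few changed sentences, and the base case will state a smaller saving. The article describes the six-month study period as under way and places the extraction a month after it ends, so at that stage the field could still be requested.

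As an optional improvement, reporting net cost per antibiotic prescription averted would make the planned comparison with published estimates independent of programme size.

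### The cost total counts only implementation and antibiotic costs, so under the stated public-payer perspective a zero change in GP visit cost is assumed, not tested

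*Protocol article*

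**What the plan says.** The protocol article builds its cost total in the Data collection section from two parts.

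- **Implementation cost:** "All resources used in implementing the package, including both consumable items and time for all personnel involved, will be identified". GP time comes from interviews: "Allocation of GP time and practice specific items will be estimated based on responses to questions in the semi-structured interviews".
- **Antibiotic cost:** "We will also estimate the economic value of the change in antimicrobial usage that results from the package using PBS list prices".

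The article then combines these two parts "to provide a measure of the total changes in costs achieved". No third part is named.

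The Data analysis section sets the viewpoint: "Cost-effectiveness of the package will be estimated from the perspective of the public healthcare system". It promises two outputs, a net implementation cost and a cost per unit fall in the prescribing rate, with one-way and probabilistic sensitivity analyses.

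On visits, the Data collection section describes the MBS as the scheme "which subsidises the costs of all visits to GPs and medical specialists in non-hospital settings". It also says that, for consenting GPs in both arms, "provider records will be obtained for each patient encounter billed to the MBS", from July 2012 to the end of the intervention. The only stated use of these records is as the offset in the prescribing-rate model.

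**The concern.** A public payer that funds both medicines and GP visits sees a change in either as a change in its costs. The plan counts the medicines and not the visits, yet calls the result a total.

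The Interventions section gives reasons why visits might move. GPs may issue delayed prescriptions, and both the communication training and the consultation booklet cover when a patient should come back. These could add return visits or save them.

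The two-part definition fixes the change in visit cost at zero. The article states this composition itself, so it is not a detail merely left to a fuller economic plan. At stake is how the net cost and the cost per unit reduction are read, since the article's Discussion presents the economic results as important to decision makers.

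**Working it through.** **No figure to reproduce.** The article gives no price per prescription, cost per visit, implementation cost or expected change in visits. The check is therefore a reading of the text plus break-even algebra. Every monetary input below is an assumption.

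**1. What is counted, against the stated perspective**

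| Cost borne by the public system | In the stated total? | Source in the article |
|---|---|---|
| Consumables and staff time for implementation | Yes | Data collection |
| GP time, as an implementation resource | Yes, from interviews in intervention practices only | Data collection; Data analysis |
| Antibiotics | Yes, at PBS list prices | Data collection |
| MBS-funded GP visits added or avoided | No | Records requested, used as offset only |

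**2. Break-even formula**

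Let I be implementation cost, R prescriptions avoided, p the list price, A = R × p the drug saving, V the net change in visits attributable to the package, and c the MBS cost per visit. I take the planned net cost to be the two-part total.

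- Planned net cost: N = I − A
- With visits: N′ = I − A + V × c
- Put s = I/A and v = V/R. N′ is zero at v* = (p/c) × (1 − s).

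A positive v* is the number of extra visits per prescription avoided that cancels an apparent saving. A negative v* is the number of avoided visits that cancels an apparent net cost.

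| p/c | s = 0.5 | s = 2 |
|---|---|---|
| 0.1 | 0.05 | −0.10 |
| 0.25 | 0.125 | −0.25 |
| 0.5 | 0.25 | −0.50 |
| 1.0 | 0.50 | −1.00 |

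When s is above 1, extra visits only enlarge a net cost that is already positive. Only avoided visits could then change the sign.

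**3. The same in dollars, per 100 encounters (all assumed)**

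- 20 antibiotic prescriptions, cut by 10%: 20 × 0.10 = 2 avoided.
- At AUD 10–20 each, the drug saving is AUD 20–40.
- At AUD 40 per visit, p/c = 10/40 to 20/40 = 0.25 to 0.5.
- Visits equal in value to the drug saving alone (s = 0): 20/40 = 0.5 to 40/40 = 1.0. At AUD 20–60 per visit the range is 20/60 = 0.33 to 40/20 = 2.0.
- With s = 0.5 and AUD 40 per visit: 2 × 0.125 = 0.25 to 2 × 0.25 = 0.5 extra visits cancel the apparent saving.
- With s = 2 and AUD 40 per visit: 2 × 0.25 = 0.5 to 2 × 0.5 = 1.0 avoided visits cancel the apparent net cost.

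**4. How precisely the trial could estimate a visit term**

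Assume a practice-level SD of 10–20% for the relative change in encounters; the article gives none. With 14 practices per arm:

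- SE = SD × √(2/14) = 3.8 to 7.6 percentage points.
- 95% half-width (t, 26 df, multiplier about 2.06) = about 8 to 16 points.
- At AUD 40 per visit: about ±AUD 310 to 620 per 100 encounters, against a drug saving of AUD 20–40.

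A shift of 0.5 to 1.0 visits per 100 encounters could matter to the payer, but the trial's encounter counts could not resolve it.

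**The case against.** **Nothing shows that visits change.** The Interventions section describes delayed prescribing and re-consultation advice without stating an effect on visit numbers. The Background reports no apparent harm to repeat consultation after enhanced communication training. This stands against any claim that the package does change visits. But that evidence concerns one component, and the Background also says the strategies had been evaluated only in isolation. It supports zero as a plausible value, not as a fixed one for the combined package.

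**The sign may never be in doubt.** Coordinator visits, training and 50 free CRP tests per practice may cost more than the drug saving. Extra visits could not then reverse the sign. This also stands. Moreover, cancelling the AUD 20–40 saving at AUD 40 per visit takes one extra visit for every two to four prescriptions avoided (2/1.0 to 2/0.5), even before any implementation cost is counted. No part of the article supports an effect of that size.

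**Longer consultations are partly costed.** GP time already enters through the interviews, so adding a change in MBS item mix could count the same minutes twice. This limits the fix. It does not bring return visits into the total.

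**A visit term is noisy and non-specific.** All-cause encounters move with working hours, leave and list size. They also miss return visits to non-consenting GPs or hospitals. This is a good reason to keep the term out of the main figure, but not to call the remainder the total.

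**Scope.** The secondary objective concerns the costs of implementing the package, which a two-part costing fits. That supports the measure under a narrower name.

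**Conclusion.** The point holds in a limited form. By its own definition, the article's cost total leaves out a cost that falls within its stated perspective and that the package could move in either direction. A zero change in visit cost is assumed and not tested. The planned sensitivity analyses are described as exploring uncertainty in the underlying data; nothing says they would add this missing category.

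A reader might infer that the net cost is biased or has the wrong sign. The documents do not support that. They give no implementation cost, prices or visit changes, so neither the direction nor the likelihood of an error can be judged. Across p/c from 0.1 to 1.0, the break-even shift is 0.05 to 0.50 extra visits per prescription avoided at s = 0.5, and 0.10 to 1.00 avoided visits at s = 2. These results rest wholly on assumed inputs.

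This is a matter of labelling plus one untested assumption in a secondary, economic analysis. The costing omission does not touch the primary effectiveness result.

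**What to change.** 1. **Rename the measure.** Call the two-part figure implementation plus antibiotic cost, and state that changes in MBS-funded GP visits are excluded.
2. **Add one scenario to the planned one-way and probabilistic sensitivity analyses.** Value the between-arm difference in the before-to-during change in MBS encounters per GP at a stated MBS benefit per visit. Report net cost with and without it.
3. **Use encounter counts, not item mix,** unless GP consultation time taken from the interviews is removed first, so that the same time is not counted twice.
4. **Keep the two-part figure as the main one.** State that the visit estimate is all-cause, not specific to acute respiratory infection, and imprecise.

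The cost is a change of wording and one extra scenario. Encounter records for both arms are already requested, and costing the change by arm needs no linkage of MBS to PBS records. The article does not say whether those records carry item numbers or benefits paid, so the benefit per visit may have to be an external input with a range. The downside is a wide interval that readers could over-interpret, which is why the scenario should be reported separately.
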